### ***Secondary analyses: Efficacy***

The following analyses of efficacy will be performed:

#### ***-Protective efficacy against clinical malaria***

- Time to first episode of malaria meeting the primary case definition of clinical malaria episode over a period of 12, and 24\* months of follow-up after the last vaccination.
- Proportion of participants with an episode of malaria meeting the primary case definition of clinical malaria episode, within the periods, 6, 12 and 24\* months of follow-up after the last vaccination (ie, from study day 63 to 243, 63 to 423, and 63 to 738, respectively)

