| Follow-up duration                                     | 26 months from Day 0                                                                                                                                                                                                                                                                                                                                                                                                                                                                                                                                                                                                                                                                                                                                                                                                                                                                                                                                                                                                                                                                                                                                                                                                                                                                                                                                                                                                                                               |

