| Blood Sampling Schedule                                | 
Phase I Lead-in Safety Evaluation: Screening, Days 0, Day 21, Day 56, Day 63, 243, 423, 783
 
Phase 2b trial: Screening, Day 0+, Day 21, Day 63, Day 243, Day 423, Day 783
 
+: nested cohort of participants only
                                                                                                                                                                                                                                                                                                                                                                                                                                                                                                                                                                                                                                                                                                                                                                                                                                                                                                                                                                                                                                                                                                                                                                                                          |

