| Primary Evaluation Endpoint: Phase 2b Trial            | Time to first episode of malaria meeting the primary case definition of clinical malaria episode ± over a period of 6 months of follow-up after the last vaccination (i.e., from study day 63 to study day 243).                                                                                                                                                                                                                                                                                                                                                                                                                                                                                                                                                                                                                                                                                                                                                                                                                                                                                                                                                                                                                                                                                                                                                                                                                                        |

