### **Ascertainment of malaria Endpoints**

Collection of malaria endpoints for analysis of efficacy will begin at Day 63, which is 7 days following of completion of the vaccination regimen.

Clinically qualified investigators will adjudicate the presence of the endpoints of clinical *P. falciparum* malaria, severe *P. falciparum* malaria, and asymptomatic *P. falciparum* carriage, before they are unblinded to Group B vs C allocation.

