#### **Safety follow-up**

Trained field workers under the supervision of the investigators will visit daily each enrolled child for days 1 to 3 post vaccination. If necessary the child will continue to be seen by the field worker on subsequent days for follow-up of adverse events. The field workers will visit the child at 30 day intervals as indicated on the Timeline of Study Visits (Table 1). In the event that the field worker finds any Grade 3 solicited general or unsolicited symptoms, the volunteer will be brought to the vaccination centre for examination by a study clinician. During the field worker visits, the children's parent(s)/guardian(s) will be asked retrospectively if any medical event that might be a SAE occurred since the last visit and this information will be recorded. Unreported SAEs detected in this way will be investigated and reported by the PI or delegate on the corresponding SAE.

If a study participant is reported to be unwell at the time of a visit, the field worker will advise the parents to report to the trial site clinic or the nearest health facility where a study nurse will be posted and will notify this referral to the clinical team for follow up. In the event that a study participant is seriously ill, the field worker will inform the PI or designate, and transport will be arranged, to the referral hospital (where a study physician is posted), if judged appropriate by the responsible clinician.

In case a study participant is unwell and referred to the trial site clinic or health facility, a duplicate blood film will be obtained should the volunteer present symptoms or signs compatible with malaria (axillary temperature  $\geq 37.5^{\circ}\text{C}$ , History of fever within the last 24 hours, loss of appetite, malaise, vomiting and diarrhoea etc).

A study clinician will review the infant at the Clinic Visits, on Days 7, 21, 56, 63, 93, 243, 363, and 723, for full safety and reactogenicity assessment.

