#### ***-Efficacy against asymptomatic *P. falciparum* infection***

- Proportion of participants meeting the primary case definition of asymptomatic *P. falciparum* infection, at study days 243, 423 and 738\*.

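### Section 9 dates two conditional 24-month efficacy analyses at Day 738, although the protocol's own day scale and visit schedule put the 24-month visit and film at Day 783; separately, the clinician review list does not match the clinic visits

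*Protocol*

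**What the plan says.** **Efficacy windows.** In Section 9 of the Protocol, under Protective efficacy against clinical malaria, the proportion of participants with an episode meeting the primary case definition is to be computed over 6, 12 and 24 months after the last vaccination. These periods are translated into study days "63 to 243, 63 to 423, and 63 to 738, respectively". The next subsection takes the proportion with asymptomatic *P. falciparum* infection "at study days 243, 423 and 738". Both 24-month entries carry the asterisk that makes them depend on the 12-month efficacy result.

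**Schedule.** The synopsis lists Phase 2b blood sampling at "Day 21, Day 63, Day 243, Day 423, Day 783" (after screening and Day 0) and gives follow-up as "26 months from Day 0". Tables 1 and 3 and the visit descriptions in Section 8 make Day 783 the final clinic visit. The tables mark a film there if the efficacy analysis is extended to 24 months; the Day 783 visit text prescribes it without that condition.

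**Clinician reviews.** The Safety follow-up text in Section 8 says that a study clinician sees the infant at the clinic visits "on Days 7, 21, 56, 63, 93, 243, 363, and 723, for full safety and reactogenicity assessment".

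**The concern.** Day 738 is in the operative definition of two secondary analyses and it appears twice, so a programmer has no reason to treat it as a slip. Followed literally, it ends one analysis labelled 24 months early, and it sets a cross-sectional survey on a day when nobody is due to be examined.

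The second consequence matters more. Asymptomatic infection can be found only by filming children who have no fever, so it needs a scheduled routine film. A child with clinical malaria, by contrast, is picked up by continuous passive detection whatever the visit days are.

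The clinician review list is a separate and smaller inconsistency. Field staff have one list of review days and another schedule of clinic visits, and the two disagree after Day 243.

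**Working it through.** **Inputs, all from the Protocol**
- Start of endpoint collection: "Collection of malaria endpoints for analysis of efficacy will begin at Day 63" (Section 8, Ascertainment of malaria Endpoints).
- The 6-month window that anchors the scale: "from study day 63 to study day 243" (synopsis, primary endpoint).
- Visit days and the ±14-day window for the later visits: Tables 1 and 3.
- Film rules and case definitions: Sections 5 and 8.

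**Step 1. Reproduce the plan's days with 30-day months from Day 63**
- 6 months: 63 + 6 × 30 = 63 + 180 = 243. Agrees.
- 12 months: 63 + 12 × 30 = 63 + 360 = 423. Agrees.
- 24 months: 63 + 24 × 30 = 63 + 720 = 783. The plan has 738.

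**Step 2. What Day 738 amounts to**
- 738 − 63 = 675 days; 675 / 30 = 22.5 thirty-day months.
- Shortfall: 783 − 738 = 45 days; 45 / 720 = 6.25% of the intended window.
- With months of 30.4375 days, Day 738 is 675 / 30.4375 = 22.2 months from Day 63 and 682 / 30.4375 = 22.4 months from Day 56. Only when counted from Day 0 does it come near 24 months (738 / 30.4375 = 24.25). The text counts from the last vaccination and starts the window at Day 63, so that origin is not available.
- Day 783 fits the stated follow-up: 783 / 30 = 26.1 months from Day 0.

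**Step 3. Is Day 738 inside any visit window?**

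| Visit | Type | Window |
|---|---|---|
| Day 723 | Home | 709 to 737 |
| Day 753 | Home | 739 to 767 |
| Day 783 | Clinic | 769 to 797 |

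Day 738 falls in the one-day gap between the two home-visit windows.

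**Step 4. Could a neighbouring home visit supply the film?** At the home visits a smear follows only if the child is febrile or has had fever in the last 24 hours. The definition of asymptomatic infection requires neither. A film triggered by that rule therefore cannot yield a case under this definition.

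**Step 5. Clinician review days against the visit schedule**
- Days 7, 21, 56, 63, 93 and 243: clinic visits in Tables 1 and 3. Six of the eight listed days agree.
- Days 363 and 723: field-worker home visits in both tables and in the visit descriptions.
- Clinic visits after Day 243: Days 423 (window 409 to 437) and 783 (window 769 to 797). Neither is on the review list. Each lies 60 days after the listed day (423 − 363 = 60; 783 − 723 = 60).

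**The case against.** The strongest reply is that 738 is a transposition of 783 and harms nothing. The same sentence calls the window 24 months, every schedule in the document says Day 783, and the table footnote ties the Day 783 film to the 24-month extension. No data collection depends on 738, and the statistical analysis plan due before unblinding could put it right. Most of this stands: the intention is hardly in doubt and trial conduct is not affected. What remains is that the wrong day is written twice in the section that defines the analyses.

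Four stronger readings are tempting, and the documents do not support them.

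- **That all 24-month analyses stop at Day 738.** Only the two quoted ones do. The time-to-event, secondary-definition, multiple-episode and severe malaria analyses give no 24-month day number. A mismatch between the 24-month proportion and the 24-month time-to-event result is therefore an inference, reached by reading the latter as 720 days.
- **That 6.25% of malaria is lost.** That figure is a share of days. With first vaccinations in March to April 2013, Days 738 to 783 run from about 9 March to 23 April 2015 for the earliest child and from 8 May to 22 June 2015 for the latest. Nearly all of this precedes the June to October peak. The endpoint is any episode since Day 63, with two peak seasons already inside the window. Transmission is year-round, so the effect is not zero, but nothing shows it to be large.
- **That 24-month asymptomatic infection cannot be measured in this trial.** A film belongs to the Day 783 visit. It is the Section 9 date that misses it.
- **That late clinical safety assessment is absent.** The Day 423 and 783 clinic visits include medical history, temperature, blood sampling and SAE recording, with examination as required. The fault is a list that disagrees with the schedule. The list also does not label Days 363 and 723 as 12 and 24-month reviews.

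**Conclusion.** The point holds in limited form. Day 738 is wrong on the protocol's own scale for two secondary analyses: the 24-month proportion with clinical malaria under the primary case definition and the 24-month asymptomatic infection survey. It falls 45 days short of the 720-day window and matches no visit. The main consequence is that the asymptomatic survey, taken literally, has no scheduled film; the change in the clinical malaria proportion is probably small.

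Both analyses run only if the 12-month result leads to extension. The primary analysis, Day 63 to Day 243, is untouched.

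The conclusion assumes 30-day months counted from Day 63, which the 6 and 12-month windows confirm exactly. The judgement that the effect on the proportion is small also assumes that the proposed 2013 vaccination dates are kept.

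The contradiction over Days 363 and 723 is real but separate. This review takes no position on which clinician review days are right.

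**What to change.** In Section 9, replace 738 by 783 in both places: the 24-month window for the proportion with clinical malaria and the day of the 24-month asymptomatic infection survey. Make the correction before the analysts are unblinded, which the Protocol allows after the 6-month data lock, so that the cut-off is not chosen with allocation known.

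Separately, reconcile the clinician review days in the Safety follow-up text with Tables 1 and 3 and the visit descriptions in Section 8, so that one set of days applies throughout.

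Four numbers are involved: 738 twice, plus the 363 and 723 entries to be reconciled. Correcting 738 adds no visit, film or analysis and does not affect the sample size. The cost of the second correction depends on which schedule the trial team confirms.

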#### ***-Efficacy against asymptomatic *P. falciparum* infection***

- Proportion of participants meeting the primary case definition of asymptomatic *P. falciparum* infection, at study days 243, 423 and 738\*.

#### ***-Efficacy against secondary case definitions of clinical malaria episode***

- Time to first episode of malaria meeting the secondary case definitions of clinical malaria episode over a period of 6, 12, and 24\* months of follow-up after the last vaccination.
- Proportion of participants with an episode of malaria meeting the secondary case definitions of clinical malaria, within a period of 6, 12 and 24\* months of follow up after the last vaccination

Time to first or only episode of clinical malaria meeting secondary endpoint definitions will be analysed as above.

Variation in efficacy over time will be examined using Schoenfeld Residuals, and time dependent covariate analysis in Cox Regression. If significant variation in efficacy over time is identified then efficacy will be presented as a summary figure over the full length of follow up, but also as a varying figure over time.

The proportion of children with asymptomatic parasitaemia at the cross-sectional surveys will be presented, and vaccine efficacy evaluated using logistic regression.

Multiple episodes of malaria will be examined using Poisson or negative binomial models on the ATP cohort (negative binomial if the data is over-dispersed) and adjusted incidence rate ratios calculated, adjusted by stratification factors. An unadjusted ITT analysis will also be conducted.

\* Depending on the outcome of the efficacy analysis of the 12 month data, this may be extended to 24 months following completion of vaccination

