## Study site

The study will take place at the Banfora trial site, which is located about 400 km from Ouagadougou, the capital city of Burkina Faso. The URC-B, the research unit is situated within the complex of the Regional hospital. The trial participants will be drawn from Banfora Health demographic system that covers a total population of 30,000 inhabitants. From recent surveys, the bed net coverage was 80%. There is no implementation of Indoor Residual Spray or IPT in infants or children in the area. To date there is no evidence of the decline in malaria incidence that has been recently reported from other parts of sub-Saharan Africa. In Burkina Faso, malaria is endemic. Transmission occurs throughout the year, with a peak during the rainy season (June to October). *P. falciparum* is responsible for more than 90% of all clinical malaria cases. The major vectors are *Anopheles gambiae*, *An. arabiensis* and *An. funestus*. Children under five years and pregnant women are the populations at highest risk. During the five months when transmission reaches a peak, individuals in these age-brackets may suffer multiple malaria episodes, with an annual malaria death toll reaching 15,000 people. In the country's hospitals, malaria is reportedly responsible for 30.7% of all hospitalization with a mortality rate of 23%.

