### ***Primary analysis***

The primary analysis of efficacy will be comparison between Group B and C of the time to first episode of malaria meeting the primary case definition of clinical malaria episode over a period of 6 months of follow up after the last vaccination (ie, from Day 63 to 243). This will be done using survival analysis (e.g. Cox proportional hazard model), adjusting for any stratification factors (age, bednet use). Results will be presented as adjusted hazard ratio with appropriate 95% confidence intervals. Vaccine efficacy will be calculated as 1-HR. Kaplan-Meier methods will be used to visualize the time to first malaria event. The primary analysis will be based on the per-protocol population. An unadjusted analysis will also be carried out on the basis of intention-to-treat.

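### Change in efficacy over time is examined only through Cox regression on first episodes, where uneven malaria risk between children can mimic waning

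*Protocol*

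**What the plan says.** The duration objective in Section 4 asks for efficacy against clinical malaria over 12 and, conditionally, 24 months. Section 9 addresses it with "Time to first episode of malaria meeting the primary case definition of clinical malaria episode over a period of 12" and conditionally 24 months, together with the proportions affected in those windows. For change over time, the protocol says "Variation in efficacy over time will be examined using Schoenfeld Residuals, and time dependent covariate analysis in Cox Regression". A significant result has a fixed consequence: "efficacy will be presented as a summary figure over the full length of follow up, but also as a varying figure over time".

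Cox regression is named in the primary analysis for time to first episode. The secondary definitions follow the same route: "Time to first or only episode of clinical malaria meeting secondary endpoint definitions will be analysed as above". Repeat episodes go elsewhere: "Multiple episodes of malaria will be examined using Poisson or negative binomial models on the ATP cohort". That model gives adjusted incidence rate ratios, and no period or vaccine-by-time term is mentioned. The protocol allows for over-dispersed counts there, and under Study site it notes that in the peak season "individuals in these age-brackets may suffer multiple malaria episodes".

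**The concern.** In a first-episode model a child leaves the risk set after one episode. The hazard ratio at any later time therefore compares only the children still episode-free. It equals per-child efficacy throughout follow-up only if children share the same underlying risk. If they do not, and the vaccine scales every child's hazard down by the same factor, high-risk children are used up faster in the control arm. The remaining controls become a lower-risk group and the ratio moves towards 1 while each vaccinated child is as well protected as before. The time-dependent covariate analysis named in the same sentence has the same property.

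The protocol expects half the controls to have had an episode by Day 243, so depletion could be substantial before the 12- and 24-month windows close. At stake is the duration conclusion: a displayed decline could be read as lost protection.

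**Working it through.** **Plan's own figures.** Section 5, Sample size: 700 children randomised 1:1, 50% and 38% with an episode by Day 243, hazard ratio 0.7. Expected events: 350 × (0.50 + 0.38) = 308. Schoenfeld power at two-sided 5% (alpha is not stated; assumed from the 95% intervals): Φ(√(308/4) × |ln 0.7| − 1.96) = 87.9%, against 88% stated. With 20% dropout, 246.4 events give 79.9%, against 80% stated. The inputs are sound.

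**Assumptions not in the documents.** Gamma-distributed child risk with mean 1 and variance θ; off-season six-month hazard 20% of the season's; second season equal to the first; no dropout; the same hazard ratio r in every child at all times, so no waning.

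**Calibration.**
- Control cumulative hazard at Day 243: Λ = (0.5^−θ − 1)/θ.
- Vaccine-arm survival at Day 243: 0.5^0.7 = 0.616, that is 38% with an episode.
- Hence r = (0.616^−θ − 1)/(θΛ).

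**Drift of the first-episode ratio.** HR(t) = r(1 + θaΛ)/(1 + θraΛ), where a = 0 at the start, 1 at Day 243, 1.2 at 12 months and 2.4 at 24 months.

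| θ | Λ | r | HR at start | Day 243 | 12 months | 24 months |
|---|---|---|---|---|---|---|
| 0.5 | 0.828 | 0.663 | 0.663 | 0.735 | 0.746 | 0.797 |
| 1 | 1.000 | 0.625 | 0.625 | 0.769 | 0.785 | 0.850 |
| 2 | 1.500 | 0.546 | 0.546 | 0.828 | 0.847 | 0.908 |

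**First-episode efficacy by year.** Efficacy is one minus the ratio of cumulative first-episode hazards, each equal to ln(1 + θkaΛ)/θ with k = r for vaccine and 1 for control. For θ = 1:
- Year 1: 1 − ln(1.749)/ln(2.2) = 29.1%.
- Year 2: 1 − ln(2.499/1.749)/ln(3.4/2.2) = 18.1%.

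The same steps give 29.4% then 22.8% for θ = 0.5, and 28.7% then 12.0% for θ = 2. Simulation under the same calibration gave 30% then 22%, 30% then 19%, and 31% then 13% for θ = 0.5, 1 and 2.

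**Rejection rate of the Schoenfeld test** (rank time, nominal 5%, 350 per arm). Ranges cover two separate simulations.

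| θ | To 12 months | To 24 months (conditional) |
|---|---|---|
| 0.5 | about 6% | about 9% |
| 1 | 9-10% | 14-16% |
| 2 | 19-20% | 32-33% |

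At θ = 0 the rates were 4.8% and 4.5%.

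**Sensitivity to the set-up.** With a per-child ratio of 0.7, a constant baseline hazard and 50% control risk at six months, the test (linear time) rejected in 6.6%, 10.8% and 12.7% of trials at 12 months for θ = 0.5, 1 and 2. At 24 months and θ = 2 the rate was about 14-18% across linear and rank time and across 50% and 41.7% control risk. The 41.7% follows from the pilot rate of 0.09 per child-month: 1 − exp(−0.54).

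**All episodes by period, same truth.** Estimated efficacy was equal in each period. The test of change, with a child-level robust variance, rejected in 4.6-6.2% of runs under the seasonal set-up and 4.7-5.4% under the constant-hazard set-up.

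**The case against.** Several objections stand.

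- No risk variance is given in the protocol. The over-dispersion wording is a contingency, not evidence of size. The cohort has a narrow age range at one site and the Cox model adjusts for age and bednet use, so only residual heterogeneity matters.
- The direction depends on proportional protection in every child. All-or-none protection would push the ratio the other way.
- The largest figures come from the 24-month efficacy analysis, which depends on the 12-month outcome. In the firm 12-month window inflation is modest at variance 0.5 to 1.
- The overall summary figure is always kept, and no sentence in the protocol formally declares waning.
- The all-episode comparison has its own bias. If each episode is assumed to lower a child's later hazard by 20%, that test rejected in 6.8%, 10.9% and 16.4% of runs at variance 0.5, 1 and 2 (months 1-12 against 13-24). At variance 1, apparent efficacy fell from 33% to 28%. First-episode hazards are not affected by immunity from in-study episodes. Replacing one analysis by the other would therefore be a trade-off.

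A further objection, that this is detail for the statistical analysis plan, does not carry. The protocol itself fixes both the method and what is reported after a significant result. That the method uses first episodes only is an inference, but Cox regression is named for nothing else.

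A reader might infer that uneven risk will produce false waning, or that a durable vaccine would appear to lose about half its efficacy in the second year. The documents support neither. The first needs both a sizeable risk variance and proportional protection. The second appears only at the top of the assumed range: at variance 0.5 and 1, year-2 efficacy is still 22.8/29.4 = 78% and 18.1/29.1 = 62% of year 1.

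**Conclusion.** The point holds in conditional form. As written, the examination of change over time has a null of constant first-episode hazard ratio, and it can mimic waning where efficacy is constant. The distortion of the displayed efficacy-over-time figure is clearer than the inflation of the test: year-2 first-episode efficacy of about 22-23%, 18-19% or 12-13% against about 30% in year 1, at variance 0.5, 1 or 2. Test inflation at 12 months ranges from slight to about four times nominal over the same range, and it depends on the baseline assumptions. These figures rest on gamma risk, proportional protection, the assumed seasonal pattern and no dropout. The primary analysis to Day 243 and the sample size are not in question. This is an inexpensive improvement to a secondary analysis.

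**What to change.** In Section 9, under the secondary efficacy analyses:

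- Keep the first-episode Cox and Schoenfeld analysis, labelled as a check of proportional hazards.
- Add beside it a vaccine-by-period comparison on all episodes: Day 63-243, Day 243-423 and, if efficacy follow-up is extended, Day 423 to the end of the 24-month window. A recurrent-event rate model, or the planned negative binomial model with counts and person-time split by period, would serve. Use a child-level robust variance.
- State that waning will be reported only if the all-episode analysis supports it, and that drift of the first-episode hazard ratio alone will not be called waning.
- Reconcile the end of the 24-month window, which is Day 738 in Section 9 and Day 783 in the visit schedule.

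The cost is analysis wording and programming, since passive surveillance already captures the episodes. A rule is needed to separate a new episode from a repeat visit or recrudescence. The all-episode ratio still includes immunity and post-treatment protection from earlier in-study episodes, so the two analyses should be read together.
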